# Trial of a prehospital intervention with traditional Chinese medicine for acute stroke (TRACE): Protocol for a mixed-methods research study

**DOI:** 10.3389/fphar.2022.879282

**Published:** 2022-08-29

**Keywords:** prehospital intervention, traditional chinese medicine, xingnaojing injection, acute stroke, study protocol, mixed methods research

## Abstract

**Background:** As the only traditional Chinese medicine injection approved by the China Food and Drug Administration for use as stroke first aid in ambulances, Xingnaojing Injection (XNJI) has been widely used in cases of both acute ischemic stroke (IS) and intracerebral hemorrhage (ICH). However, there is no robust clinical evidence regarding the efficacy and safety of the early use of XNJI during stroke first aid. The main purpose of this trial is to observe whether XNJI, intravenously administered within 24 h of onset in the prehospital ambulance setting, protects against early neurological deterioration (END) on the third day of onset in patients with acute stroke.

**Methods:** The Trial of a prehospital intervention with traditional Chinese medicine for acute stroke (TRACE) is a Mixed-Methods research (MMR) study that involves a combination of quantitative and qualitative research. The quantitative research part of this project is a prospective, multicenter, observational, clinical registry study, for which we aimed to recruit 1,000 patients with acute stroke (IS and ICH). Based on our observation of whether XNJI was intravenously administered within 24 h of onset in the prehospital ambulance setting, patients with acute stroke will be divided into two groups: the exposure group comprising patients who were intravenously administered XNJI and the nonexposure group comprising patients who were not. The primary outcome is early neurological deterioration (END) on the third day of onset defined as an increase of 2 or more points in the National Institute of Health Stroke Scale score between baseline and day 3. In addition, based on the aforementioned quantitative research, qualitative research will be conducted by interviewing emergency doctors about their knowledge and attitude regarding XNJI used for stroke first aid.

**Discussion:** The results of the TRACE study will provide preliminary evidence for the relationship between XNJI used within 24 h of onset and the presence of END on the third day after stroke onset; it will aid in improving the current knowledge regarding the early use of XNJI for stroke first aid.

**Clinical Trial Registration:**
clinicaltrials.gov, identifier NCT04275349

## Introduction

Stroke is the first cause of death and disability among adults in China and the second leading cause of death worldwide (Group, 2020). In 2019, among all the subtypes of stroke, ischaemic stroke (IS) had a prevalence of 62.4%, and intracerebral brain hemorrhage (ICH), of 27.9% (GBD 2019 Stroke Collaborators, 2021). Stroke, a life-threatening disease, often leads to severe central nervous system damage in case of untimely treatment (Saver, 2006; Chen et al., 2019). Early neurological deterioration (END) is a frequent and serious complication of acute stroke, with an incidence of 5%–40% (Thanvi et al., 2008; Geng et al., 2017). It is characterized by progressive deterioration of neurological function within 48-72 h after stroke (Celik et al., 2019; Kang et al., 2021). END is strongly associated with an increased risk of functional disability, mortality, and poor 3-month clinical outcomes (Kwan and Hand, 2006; Geng et al., 2017). Currently, vascular recanalization strategies, including intravenous thrombolysis (IVT) and endovascular therapy (EVT), are recommended first-line therapy options for acute ischemic stroke (AIS) (Ma et al., 2019; Powers et al., 2019). However, they only benefit a small number of patients due to narrow time windows, imaging dependence, high risk of bleeding, and limited repass rates (Wang et al., 2019). The treatment options for ICH are also limited (Schrag and Kirshner, 2020). There are no specific drugs for treating ICH, and the benefits and risks of surgical treatment are controversial (Deng and Wu, 2021; Zhang and Zhou, 2022)).

Xingnaojing injection (XNJI) is made using an extract from the An Gong Niu Huang pill, a popular and effective first-aid TCM used for acute stroke, which has been clinically applied for more than 200 years (Deng et al., 2010; Wang, 2022; Wang W. et al., 2022). Using modern pharmaceutical technology, dangerous ingredients, such as cinnabar and realgar, are removed, and four ingredients including musk, gardenia, Yujin, and borneol are retained and refined to obtain a convenient and effective water-soluble intravenous injection (Yue et al., 2019). Many studies have demonstrated the effectiveness and safety of XNJI for acute stroke (Ma et al., 2013; Shen et al., 2020; Wang et al., 2021), and the guidelines and consensus in China have recommended the use of XNJI as stroke first aid (Gao, 2016; Department of Neurology, 2018).

However, on conducting an overview of systematic reviews and meta-analyses (Tian et al., 2021), we found that none of the included studies reported on the different medication timings of XNJI use in acute stroke and on stroke severity. We also conducted a mixed-methods research (MMR) study (Tian, 2021) and found that early XNJI use within 6 h of stroke onset maybe associated with greater functional improvement. However, the appropriate initiation time of XNJI treatment is also unclear due to medical insurance restrictions and concerns regarding possible incompatibility between XNJI and IVT. A recent systematic review and meta-analysis (Wang L. et al., 2022) have also suggested that the optimum XNJI initiation time during the acute phase might be within the first 72 h after stroke onset, preferably within the first 6 h. However, due to insufficient evidence, it remains unknown whether XNJI should ideally be administered immediately after stroke onset or within 24 h. In addition, in real-world settings, the knowledge and attitude of emergency doctors regarding XNJI used for stroke first aid are also very critical. Therefore, we designed this MMR study to explore the relationship between XNJI used within 24 h of onset and the presence of END 3 days after symptom onset in patients with acute stroke.

## Methods and analysis

### Study design

The Trial of a prehospital intervention with traditional Chinese medicine for acute stroke (TRACE) study (registered with ClinicalTrials.gov, ID: NCT04275349) will be designed as an MMR study aimed at exploring the relationship of XNJI used within 24 h of onset with the presence of END on the third day after symptom onset in patients with acute stroke. We will compare the presence of END on the third day after stroke onset between the exposure group and the nonexposure group. An overview of the study flowchart is presented in Figure 1. The registry protocol was approved by the Ethics Committee of Dongzhimen Hospital Affiliated with Beijing University of Chinese Medicine, Beijing, China (Approval number: DZMEC-KY-2019-153), and will be approved based on the requirements of the local institutional review boards of all the participating sites.

**FIGURE 1 F1:**
[figure not shown]
Flowchart of the TRACE study. Abbreviations: TRACE, Trial of a prehospital intervention with traditional Chinese medicine for acute stroke; BEFAST, Balance-Eyes-Face-Arms-Speech-Time; XNJI, Xingnaojing Injection; NIHSS, National Institutes of Health Stroke Scale; CT, Computed Tomography; MRI, Magnetic Resonance Imaging; ICH, intracerebral hemorrhage; BI, Barthel Index; mRS, modified Rankin Scale.

### Recruitment

Patients will be recruited consecutively from 20 participating sites, including both Western medicine hospitals and TCM hospitals in Beijing, China, which have the capability of conducting qualified research and express a proven commitment to the study. The recruitment started in March 2018 and is estimated to end in December 2022. Eligible adult patients with suspected acute stroke within 24 h of onset will be sent to the hospital by ambulance. We plan to recruit 1,000 patients with confirmed acute stroke based on the inclusion and rejection criteria. The time of stroke onset was defined as the time at which the patient was last observed to be well. Only those who meet the inclusion criteria and willingly provide written informed consent will be recruited. Since this is an observational study that involves a specific prehospital emergency intervention, it is difficult to obtain written informed consent from the patient in the prehospital ambulance setting. The patient will be asked to sign a written informed consent form in the hospital. The researchers will inform patients of the benefits and risks of participating in the research and of the need to analyze their prehospital information in addition to their in-hospital information; they will also be assured that this will not interfere with the actual clinical diagnosis and treatment. Legal guardians will sign the informed consent form on behalf of patients in a coma. If the patient or his legal guardian does not agree to the use of the diagnosis and treatment-related information in this study, the prehospital information will not be used. The participation of patients will be entirely voluntary, and their data will be strictly protected to the extent permitted by the law.

In this study, to increase the rate of identifying suspected stroke patients, the prehospital assessment scale for identifying these patients was changed from the Face-Arms-Speech-Time (FAST) scale to the Balance-Eyes-Face-Arms-Speech-Time (BEFAST) scale. Once meeting the inclusion criteria, patients will be included and registered immediately in an ambulance. However, due to the busy task and high tension in the prehospital ambulance setting, ambulance doctors are unable to exclude patients in detail. The ineligible patients will be rejected after admission. Therefore, this study has changed the exclusion criterion to the rejection criterion. 

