
### Sample size calculation

According to the definition of the dominant population, at least one particular subgroup will have a positive outcome in terms of the primary efficacy index. A previous study conducted in Germany reported that approximately 13% of patients exhibited END on the third day after stroke onset (an increase of 2 or more points in the NIHSS score). Data obtained from our previous research as well as other domestic research showed that the rate of END on the third day after stroke onset was approximately 6–8%. The sample size was calculated on the following assumptions: the END rate in patients who did not receive the TCM intervention was 13% based on data from studies conducted overseas, and the END rate in patients who received the TCM intervention was 7% based on domestic data. Since there is no formula meant specifically for calculating the sample size in registry studies, we decided to use the one-sided difference test based on the statistical analysis method and formula for calculating the sample size in cohort studies. Consequently, the following formula, where α = 0.05 and β = 0.2, was used:
$$\text{n}={\left[\frac{Z_{1}-\alpha \sqrt{2\text{pq}}+Z_{1}-\beta \sqrt{{\text{p}}_{1}\left(1-{\text{p}}_{1}\right)+{\text{p}}_{2}\left(1-{\text{p}}_{2}\right)}}{{\text{p}}_{1}{-\text{p}}_{2}}\right]}^{2}.$$

The smallest sample size for a single cohort was estimated to be 426 patients; therefore, a minimum of 852 patients must be included. Considering the uneven distribution of exposure factors among patients and the inability of some patients to attend all the visits through the 90 days, the sample size was increased to 1,000 cases, which is an increase of 17% on the original base size.

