### Data processing and analysis

The mean (Mean), standard mean difference (SD), median (Median), interquartile ranges, minimum (Min), and maximum (Max) will be used to summarize continuous data, while rate or percentage will be used for categorical data. Between-group comparisons will be conducted using parametric or non-parametric tests, as appropriate. Pearson’s chi-squared test is used for the count data, and the results are expressed as rate or percentage (%). Measured data, if data are normally distributed and the variance is homogeneous, the parametric test (*t*-test) will be used and results will be expressed as mean ± SD; If the data are not normally distributed and still do not meet the requirements for the parametric test after data conversion, the non-parametric test (Wilcoxon rank sum test or Mann-Whitney U test) will be used and results will be expressed as median (Median).

As the primary analysis, a comparison of the presence of END on the third day after stroke onset will be conducted between the two groups of patients—the exposure group and the nonexposure group—using Pearson’s chi-squared test. The secondary outcome analyses will involve the rate of stroke-related and any-cause deaths, differences in the NIHISS scores, differences in the ICH scale scores, proportion of patients with BI scores ≥90, and proportion of patients with mRS scores ≤2. These analyses will be performed according to the standard statistical principles for comparing parametric or non-parametric distributions, as appropriate. During the analysis, multivariate linear regression analysis is performed for the influencing factors that are statistically significant in the univariate analysis. The full analysis set will be used in the efficacy correlation analysis in this study. The safety analysis set will be used in the safety analysis. The full analysis set refers to the set of eligible cases and detached cases but not eliminated cases. The safety analysis set will consist of safety indicators for all enrolled subjects with post-medication safety evaluation data; the number of subjects with missing data will be reported. All statistical tests will be one-sided, and statistical significance will be set at *p* < 0.05. SAS software, version 9.2 (SAS Institute, Inc., Cary, NC, United States), will be used to perform the statistical analyses.

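### The primary chi-squared test pools 20 hospitals and ignores site; if both XNJI use and END vary by hospital, the one-sided 5% level is not assured and site confounds the comparison.

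*Protocol article*

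**What the plan says.** All of this is in the protocol article.

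- **Recruitment.** "Patients will be recruited consecutively from 20 participating sites, including both Western medicine hospitals and TCM hospitals".
- **Data processing and analysis.** "As the primary analysis, a comparison of the presence of END on the third day after stroke onset will be conducted" between exposed and nonexposed patients "using Pearson’s chi-squared test". On direction and level: "All statistical tests will be one-sided, and statistical significance will be set at" p < 0.05. The only regression mentioned is linear, restricted to factors significant in univariate analysis, and does not name site.
- **Sample size calculation.** The formula is for independent patients: "we decided to use the one-sided difference test", "where α = 0.05 and β = 0.2, was used", with END rates of 13% (nonexposed) and 7% (exposed). This is said to give 426 per cohort, 852 in all. Then "the sample size was increased to 1,000 cases, which is an increase of 17% on the original base size", explained by uneven exposure and missed visits. Clustering is not among the reasons.
- **Intervention measures.** Exposure is whether XNJI was given in the ambulance. Later care is left to the treating clinicians.
- **Data collection and management.** In-hospital NIHSS is scored by researchers appointed at each site.
- **Quality control and monitoring.** Possible heterogeneity between centres is acknowledged and answered with training and audit.

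**The concern.** A pooled chi-squared test has its stated error rate only if patients are independent given their exposure group. The design gives reasons to doubt that.

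- **Outcome.** END is a change in a score rated by each hospital's own researchers, under local care. The note to Table 2 lets the baseline score come from the ambulance or from after admission, and that practice may differ by site.
- **Exposure.** XNJI use is observed, not assigned. The Introduction calls emergency doctors' knowledge and attitude critical, and the qualitative part is built around them. The hospitals are of two kinds, Western medicine and TCM.

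If hospitals differ in both the share of exposed patients and the END rate, two things follow. The between-hospital part of the comparison varies more than the chi-squared variance allows, so a null effect is declared significant too often. Any systematic link between the two, for example by hospital type, also biases the comparison. Adjusting for patient-level covariates does not by itself repair the standard error if correlation within site remains.

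**Working it through.** **Inputs from the document:** 1,000 patients, 20 sites, one-sided 5%, power 80%, END 13% versus 7%.

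**Assumptions, because the document gives no figure:** equal sites, so m = 1,000/20 = 50; exposed share 50%; exposure ICC (ρx) 0.1 to 0.5; outcome ICC (ρy) 0.01 to 0.05.

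**1. The plan's own sample size.** The printed formula with mean rate 10%, z = 1.645 and z = 0.842 gives [1.645·√0.18 + 0.842·√(0.1131 + 0.0651)]² / 0.06² = 308.1, so 309 per cohort. The stated 426 is not reproduced; it corresponds to about 90% power (426.3 unrounded). That is a separate matter, but it means 1,000 patients in two groups of 500 have 93.6% one-sided power under independence.

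**2. Actual level of the pooled test.** For an exposure that varies within and between sites:

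DE = 1 + (m − 1)·ρx·ρy; actual one-sided error = 1 − Φ(1.645/√DE); effective N = 1,000/DE.

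Example, ρx = 0.3 and ρy = 0.02: DE = 1 + 49 × 0.006 = 1.294; 1.645/√1.294 = 1.446; error 7.4%.

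| ρx | ρy | DE | One-sided error | Power at effective N |
|---|---|---|---|---|
| 0 | any | 1.000 | 5.0% | 93.6% |
| 0.1 | 0.01 | 1.049 | 5.4% | 92.6% |
| 0.1 | 0.02 | 1.098 | 5.8% | 91.6% |
| 0.1 | 0.05 | 1.245 | 7.0% | 88.4% |
| 0.3 | 0.01 | 1.147 | 6.2% | 90.6% |
| 0.3 | 0.02 | 1.294 | 7.4% | 87.3% |
| 0.3 | 0.05 | 1.735 | 10.6% | 77.6% |
| 0.5 | 0.01 | 1.245 | 7.0% | 88.4% |
| 0.5 | 0.02 | 1.490 | 8.9% | 82.9% |
| 0.5 | 0.05 | 2.225 | 13.5% | 68.4% |

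The power column is for a test held at 5% with the effective N split equally.

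**3. Where power reaches 80%.** This needs 308.1 per group, so DE = 500/308.1 = 1.62.

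**4. Simulation of the level.** Beta-binomial, 20 sites of 50, no effect, END 10% or 13%, 40,000 runs per setting. The pooled test rejected in 4.9% to 5.2% of runs with ρx = 0, 6.1% to 6.2% at 0.3/0.01, 8.9% to 9.0% at 0.5/0.02, and 13.0% to 13.3% at 0.5/0.05. This agrees with the formula.

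**5. Level and cost of stratifying.** A hospital-stratified test uses only within-hospital contrasts, about 20 × 49 × (1 − ρx) = 980·(1 − ρx) patients' worth of information. At ρx = 0.3 that is 686, or 343 per group, with power about 84%. At ρx = 0.5 it is 490, or 245 per group, with power about 72%. A simulation of the Cochran-Mantel-Haenszel test in the same layout (ρy 0.01 and 0.05) gave a one-sided level of 4.8% to 5.2% throughout. Its power was about 91%, 84% and 72% at ρx = 0.1, 0.3 and 0.5.

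**The case against.** The strongest reply is that inflation needs exposure and outcome to cluster by the same unit, and the article shows neither. XNJI is given or withheld before the patient reaches hospital, and nothing says its use differs by receiving hospital. If it does not, the level stays at 5% whatever the outcome ICC. The ambulance doctor or crew may be the more natural cluster, and a hospital term need not remove clustering at that level. This stands, and it makes the point conditional.

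It may also be said that handling of centre belongs in the statistical analysis plan, which is not shown. That plan may add a site-adjusted sensitivity analysis. But the article itself names the primary test, and the named test has no site term, so this is not a complaint about something left out.

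Four stronger readings are tempting and not supported:

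- **That the 5% level is certainly missed.** It is not assured; whether it is missed depends on ICCs nobody has reported.
- **That exposure is fixed by hospital.** With ρx = 1 and ρy = 0.05 the formula gives 18.8% error and an effective N of 290. That would require each hospital to receive only treated or only untreated patients, which fits badly with case-by-case use in ambulances. A hospital fixed effect or stratified test could not then estimate the effect at all.
- **That power falls below plan.** Over most of the range it does not, because 1,000 patients exceed what the stated inputs need.
- **That the confidence interval is too narrow.** The article states a test for the primary comparison and no interval.

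**Conclusion.** The point holds as a conditional risk. The primary test ignores site in an observational comparison across 20 hospitals of two kinds, with locally rated outcomes and acknowledged between-centre heterogeneity. Over the assumed ICC range the one-sided error runs from about 5.4% to 13.5%, with moderate values giving 6% to 7.5%; without clustering of exposure there is no inflation. Of the nine clustered settings tabulated, only the two with outcome ICC 0.05 and exposure ICC 0.3 or 0.5 take power below 80%.

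These figures rest on equal sites, equal exposure groups and assumed ICCs. The plan itself expects uneven exposure, which would lower power further. They cover only the variance; bias from site confounding comes on top and cannot be sized from the documents. A stratified primary test is a better choice than the stated one and is cheap to adopt.

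**What to change.** Before database lock, and without reference to outcome by exposure group:

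1. Make the primary test of END hospital-stratified: a Cochran-Mantel-Haenszel test, or a logistic model with a hospital effect.
2. State in advance how small hospitals, or those with only exposed or only unexposed patients, are handled: a random hospital effect, or pooling within hospital type (Western medicine or TCM).
3. If a cluster-robust variance is used, apply a small-sample correction, since there are only 20 clusters.
4. Table 1 lists no ambulance crew or station identifier. If one exists elsewhere in the data, check clustering at that level as a sensitivity analysis.
5. Keep the pooled chi-squared test as descriptive, and report the exposed share and END rate by hospital.

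**Cost.** No new patients or visits are needed, and the hospital is known because its own researchers enter the data. The price is precision. It is negligible if XNJI use is similar across hospitals and grows as use becomes concentrated: under the assumptions above, power is about 84% at exposure ICC 0.3 and 72% at 0.5. Hospitals with a single exposure status add little to the stratified estimate. A random effect recovers some of their information, at the price of assuming that hospital effects are unrelated to exposure.

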### Rejection criteria

•Other diseases that lead to motor dysfunction (e.g., claudication, severe osteoarthritis, rheumatoid arthritis, and gouty arthritis)•Other diseases or psychosis that renders outcome assessments or follow-up unlikely to be possible•Known to be pregnant or lactating•Non-acute stroke [result from Computed Tomography (CT) or Magnetic Resonance Imaging (MRI)].

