### Intervention measures

The quantitative research part of this study will be observational. Based on our observation of whether XNJI was intravenously administered within 24 h of onset in the prehospital ambulance setting, patients with acute stroke will be divided into two groups: the exposure group comprising patients who were intravenously administered XNJI and the nonexposure group comprising patients who were not. During the study period, all relevant data will be collected at the following timepoints to facilitate a continuous dynamic observation and evaluation: during the prehospital ambulance service; within 24 h of admission; day 3 after stroke onset; day 10 after stroke onset or the day of discharge; and 30 ± 3, 60 ± 3, and 90 ± 7 days after stroke onset. This research will not interfere with the actual diagnosis and treatment of the participants. The clinicians will make decisions regarding routine treatment options based on the patient’s specific circumstances. The routine stroke treatment will follow the current national guidelines for acute Is and ICH from the Chinese Society of Neurology.

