
### Follow-up procedures

Independent interviewers with a background in neurology will be trained in a standard operating procedure (SOP) for contacting patients. The interviewers will regularly follow up with the patients over the telephone using standard interview forms in the eCRF at 30 ± 3, 60 ± 3, and 90 ± 7 days after stroke onset. The standard interview forms in the eCRF include the mRS, BI, basic medication-related questions, and rehabilitation-related questions. All interviews will be recorded and saved. Patients will have the right to withdraw from the trial at any time without reason, punishment, or loss of interest, and their medical treatments will not be affected. Participants who do not formally withdraw from the trial but no longer attend follow-up sessions will also be regarded as having withdrawn from the trial. The data of these participants will be considered valid and will not be replaced. While respecting the individual rights of the participants, researchers should try their best to understand the reasons for withdrawal to better protect the participants. The participants who drop out due to AEs should be followed up until their physical status is stable, while the other participants who dropped out should not be followed up.

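### One rejection criterion is judged after XNJI exposure is on record, is not limited to pre-stroke conditions, and removes confirmed strokes from the efficacy analysis

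*Protocol article*

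**What the plan says.** Entry takes place in the ambulance, on three inclusion criteria (Recruitment; Inclusion criteria): "Once meeting the inclusion criteria, patients will be included and registered immediately in an ambulance". Exposure is settled in the same place. Intervention measures forms the groups by "whether XNJI was intravenously administered within 24 h of onset in the prehospital ambulance setting", and Data collection and management closes the prehospital record to change at admission.

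Eligibility is checked afterwards: "The ineligible patients will be rejected after admission. Therefore, this study has changed the exclusion criterion to the rejection criterion". The reason given is that ambulance doctors cannot screen in detail.

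There are four rejection criteria: other disease causing motor dysfunction, pregnancy or lactation, imaging that shows no acute stroke, and "Other diseases or psychosis that renders outcome assessments or follow-up unlikely to be possible".

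Efficacy is analysed in the full analysis set (Data processing and analysis): "The full analysis set refers to the set of eligible cases and detached cases but not eliminated cases". Patients who simply stop attending are treated differently. Follow-up procedures counts them as withdrawn but says "The data of these participants will be considered valid and will not be replaced".

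**The concern.** Whether a patient is analysed should not depend on a judgement made after the exposure whose effect is being estimated, unless that judgement concerns a fact fixed beforehand. Three of the criteria broadly meet this test. The fourth does not. It asks someone at the receiving hospital to predict whether outcome assessment or follow-up will be possible, and it does not say that the disease or psychosis must predate the stroke.

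The study is observational and XNJI use is already recorded, so the judgement is made with exposure knowable. Patients judged unlikely to be assessable are plausibly sicker and at higher risk of END. If they are rejected more often in one group, the END rates differ for a reason unrelated to XNJI. Adjusting for baseline covariates does not repair this, because the rejected patients are outside the analysis set.

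**Working it through.** **Order of events**

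1. Registration, in the ambulance (Recruitment).
2. XNJI given or not given, in the ambulance (Intervention measures).
3. Prehospital record closed at admission (Data collection and management).
4. Rejection, after admission (Recruitment).
5. Primary outcome, NIHSS change to day 3 (Types of outcomes).
6. Efficacy set: eligible and detached cases, not eliminated ones (Data processing and analysis).

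The article uses *rejected* in one place and *eliminated* in another. Treating them as the same is an inference, but the conclusion does not depend on it. Rejected patients are called ineligible and the set is built from eligible cases, so they leave on either reading.

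**Illustration of size**

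The plan gives no rejection rate, so there is no figure of its own to reproduce. Inputs from the article: END rates of 13% and 7%, a total of 1,000, and one-sided tests at 0.05 (Sample size calculation; Data processing and analysis). Assumptions: 500 per group before rejection (the article itself expects uneven exposure), no true drug effect, and END cases rejected in the exposed group only.

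With counts at 13%, each group has 0.13 × 500 = 65 END cases.

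- 10 rejected: 55/490 = 11.2%. The difference is 1.8 points. The pooled rate is 120/990 = 0.1212 and the standard error is √[0.1212 × 0.8788 × (1/490 + 1/500)] = 0.0207, so z = 0.0178/0.0207 = 0.86.
- 20 rejected: 45/480 = 9.4%. The difference is 3.6 points. The pooled rate is 110/980 = 0.1122 and the standard error is 0.0202, so z = 0.03625/0.0202 = 1.80, above 1.645. This needs 20/65 = 31% of one group's END cases rejected and none of the other's.

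In general, if a share f of END cases is rejected, the observed rate is p(1 − f)/(1 − pf). The chance of a significant one-sided result is Φ[(p − p_obs − 1.645·SE_pooled)/SE_unpooled].

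| True END rate, both groups | Share of exposed END cases rejected | Patients | Observed exposed rate | Chance of a significant result |
|---|---|---|---|---|
| 13% | 0 | 0 | 13.0% | 5% |
| 13% | 10% | 6.5 | 11.9% | 14% |
| 13% | 20% | 13 | 10.7% | 30% |
| 13% | 30% | 19.5 | 9.5% | 54% |
| 7% | 10% | 3.5 | 6.3% | 11% |
| 7% | 20% | 7 | 5.7% | 21% |
| 7% | 30% | 10.5 | 5.0% | 37% |

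To turn a true 13% into the planned 7%, solve (65 − r)/(500 − r) = 0.07. This gives r = (65 − 35)/0.93 ≈ 32 patients, or 6.5% of the group and about half its END cases.

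If the same share were rejected in both groups, the observed rates would stay equal and no false difference would arise. Rejection concentrated in the nonexposed group would act against XNJI. The direction is therefore open as well as the size.

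**The case against.** The strongest reply is that these are ordinary baseline exclusions postponed because an ambulance is a poor place to apply them. For motor disease, pregnancy or lactation, and non-acute stroke on imaging, that reply stands. Confirming such facts late introduces little bias.

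Two stronger readings are tempting, and the article does not support either.

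- A reader might infer that a patient who worsens and develops lung infection or kidney failure would be rejected. Table 1 lists both as complications recorded at the in-hospital visits, that is, in patients who remain. In-hospital death is a secondary outcome, and comatose patients can enter through a guardian's consent. Stroke deterioration itself is not a rejection reason.
- A reader might infer that a patient whose deficit clears would be rejected as not having an acute stroke. That criterion rests on the CT or MRI result, not on recovery.

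It is also fair to say that a condensed article may leave the timing of rejection and a table of rejections to fuller documents, and that the audits of registration standards under Quality control and monitoring may narrow discretion. The absence of a deadline or table alone would not be a finding. What remains is a rule the article does state: an open-ended criterion, applied after exposure, together with an efficacy set that leaves out those it removes. Auditing adherence to an open-ended criterion does not close it.

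**Conclusion.** The point holds for the second rejection criterion only. As written, it lets a judgement made after exposure, with XNJI use on record, remove imaging-confirmed strokes from the efficacy analysis. The END comparison is biased if those rejections are related to END and differ by exposure group. Nothing in the article shows that they do.

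The size is unknown. The calculations show only that small numbers could matter: 1.3% of a group, if all were END cases and all in the exposed group, would raise a nominal 5% error to about 14%. A reader might take the z of 1.80 as a sign that a false positive is likely. It is not, because it requires 31% of one group's END cases to be rejected and none of the other's, a share no document supports. The 500 per group split is also assumed.

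**What to change.** 1. Restrict this criterion to diseases or psychosis present before stroke onset. Leave the other three as they are.
2. For patients still to be enrolled, decide it at admission and before the day-3 NIHSS. This can reach few patients. Recruitment was planned from March 2018 to December 2022, 58 months, and the article appeared at the end of August 2022, with four months left.
3. Define the full analysis set to keep every consenting patient with an imaging-confirmed acute stroke who is not rejected on a pre-stroke condition, and use one term for rejected and eliminated cases.
4. Report the number rejected by exposure group and reason.
5. Run a sensitivity analysis of END that returns consenting patients already rejected under this criterion. Use the day-3 NIHSS where it exists. Where it does not, set END to give the best case and then the worst case for XNJI.

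The cost is amended wording in two sections, one extra table and one extra analysis. The downside is somewhat more missing outcome data. The article does not say whether a day-3 NIHSS is collected after rejection, so the best-case and worst-case limits may be wide.
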